### Data analyses

#### Sample size and statistical power

Simulation-based sample size calculations [38] were used to determine an adequate sample size to detect the change associated with the intervention using the primary outcome. Information used in the simulation, including the effect size, were derived from a previous study estimating the incidence and impact of non-beneficial treatment in three Queensland tertiary public hospitals [22].

Weekly identification of at least three at-risk patients in each of the 21 clinical teams across the 3 hospitals will give a statistical power of 95% to detect a reduction in the proportions of patients with ICU admissions from 0.20 in the usual care exposure period to 0.113 in the intervention exposure period. The sample size calculations were based on a 5% statistical significance level for a two-sided test, within-ward correlation of 0.1, and a stepped-wedge design as shown in Fig. 1. We performed a sensitivity analysis with an alternative within-ward correlation of 0.01 and estimated the power to be 79.3%.

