## Discussion

The emphasis of this study is to support clinicians to recognise the potential for non-beneficial treatment at the end of life using a feedback loop that relays objective information about risk profiles in relation to death and deterioration. The tailored clinical response promotes communication, engagement and awareness. Audit and peer feedback approaches have been considered promising for over two decades in areas such as improving the accuracy of clinical documentation [44] and potentially assisting in clinician’s behaviour change [45].

The expected benefits are improved patient outcomes in terms of reduction in non-beneficial treatments following the clinical team response to the patient record review data, specifically the CriSTAL and SPICT scores and indicators. This should facilitate planning and delivering appropriate care and treatment to those patient groups. Cost savings may be observed due to the prevention of non-beneficial treatments. In addition, the qualitative process evaluation will identify key factors to the intervention’s implementation and performance, as well as the potential to be implemented at other hospitals, in line with best-practice recommendations for these interventional trials [30, 46].

The stepped-wedge design used has several strengths. The incremental roll-out of the stepped-wedge design is practical to implement, mimics how the intervention might be implemented in practice at other hospitals [47] and is well-suited to the evaluation of health service delivery interventions [43]. This design allows the study team to work with each hospital during the intervention establishment phase. Each hospital contributes data to both the control and intervention conditions, mitigating risk associated with comparing heterogeneous hospitals. This crossover also means that temporal effects can be studied [48] with more efficiency than other cluster designs [49]. The risk of contamination between sites and teams is minimised by geographical separation of sites and simultaneous crossover of clinical teams within the same site. The main drawbacks of this design are the potential risk of secular trends unrelated to the intervention exposure, and risk of unequal exposure to seasonal trends. These risks were taken into consideration in the statistical analysis plan.

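### The two stated powers, 95% at a within-ward correlation of 0.1 and 79.3% at 0.01, differ by more than the correlation alone can explain

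*Protocol article*

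**What the plan says.** All the figures are in the protocol article under Sample size and statistical power.

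- Recruitment: "Weekly identification of at least three at-risk patients in each of the 21 clinical teams across the 3 hospitals".
- Main claim: this recruitment "will give a statistical power of 95% to detect a reduction in the proportions of patients with ICU admissions".
- Effect assumed in that claim: a fall "from 0.20 in the usual care exposure period to 0.113 in the intervention exposure period".
- Test and base-case correlation: "5% statistical significance level for a two-sided test, within-ward correlation of 0.1", with the stepped-wedge layout of Fig. 1.
- Sensitivity run: "We performed a sensitivity analysis with an alternative within-ward correlation of 0.01 and estimated the power to be 79.3" per cent.
- Method: "Simulation-based sample size calculations [38] were used to determine an adequate sample size".

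The correlation is the only input that the text says was varied. The Discussion describes "simultaneous crossover of clinical teams within the same site", so there are three crossover sequences of seven teams, and each hospital contributes data to both conditions. Analysis of primary outcome plans a mixed binomial regression with a random intercept per team, a random slope for the intervention, a linear time term, age and sex.

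**The concern.** A tenfold smaller correlation is reported to cost 15.7 points of power (95 − 79.3). In a parallel cluster trial a smaller correlation raises power. In a stepped-wedge trial most of the comparison is within team, so the correlation should matter little in either direction. A loss of this size fits neither case.

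This paragraph is the article's only justification of the sample size. If the base-case figure is the wrong one, the type II error at the planned assumption could be well above the 5% implied. Anyone interpreting a null result on ICU admission would then be relying on a wrong number.

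**Working it through.** **Inputs from the article.** 21 teams in 3 sequences; 3 patients per team per week; proportions 0.20 and 0.113 (mean 0.1565); two-sided 5%; correlations 0.1 and 0.01.

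**Assumed.** Stage lengths, because Fig. 1 is not shown. Step 2 does not depend on them.

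**Step 1. What the stated pair requires.** Power ≈ Φ(δ/SE − 1.96), so δ/SE = 1.96 + z(power).
- 95%: 1.960 + 1.645 = 3.605
- 79.3%: 1.960 + 0.817 = 2.777
- Ratio of squared noncentralities: (3.605/2.777)² = 1.685

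**Step 2. The most the correlation can supply.** With fixed total variance σ², the covariance within a team is V(ρ) = σ²[(1 − ρ)I + ρJ], where J is the all-ones matrix. Then V(0.1) − (0.90/0.99)·V(0.01) = σ²(0.1 − 0.0091)J, which is non-negative definite. The variance of the effect estimate at 0.1 is therefore at least 0.90/0.99 = 0.909 of that at 0.01, and the squared noncentrality can rise by at most 0.99/0.90 = 1.10. This holds for any schedule and any set of time terms. A random slope with the same variance in both runs only adds a further non-negative term.

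**Step 3. What each figure implies for the other.**
- If 95% at 0.1 is right, power at 0.01 ≥ Φ(3.605 × √(0.90/0.99) − 1.96) = Φ(1.477) = 93.0%.
- If 79.3% at 0.01 is right, power at 0.1 ≤ Φ(2.777 × √1.10 − 1.96) = Φ(0.952) = 83.0%.

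**Step 4. Trying to reproduce the figures.** Generalised least squares variance, random team intercept, linear time, assumed schedules:

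| Assumed schedule | Power at 0.01 | Power at 0.1 |
|---|---|---|
| 60 weeks, no gap | 99.5% | 99.2% |
| 60 weeks, 8-week establishment gap | 95.9% | 94.1% |
| 40 weeks, 4-week gap | 90.5% | 86.9% |
| 24 weeks, no gap | 84.8% | 80.5% |

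The base-case 95% is nearly reproduced in the second row, but the same row gives 95.9% at 0.01, not 79.3%.

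A search covered 7,500 combinations of schedule and time term (8 to 70 weeks, gaps of 0 to 12 weeks; no, linear or categorical time). The largest gain from 0.01 to 0.1 was 4.0 points and the largest squared-noncentrality ratio was 1.10. The nearest pair was 85.8% at 0.01 and 88.8% at 0.1, which is 6.5 points from the stated 79.3% and 6.2 from the stated 95%.

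**Step 5. Binomial scale.** Logistic simulation with team effects and linear time (600 runs per cell, latent-scale ICC) gave, at 0.01 / 0.1: 90.5% / 92.3%, 83.3% / 84.7% and 71.8% / 78.5% for three schedules. The largest gap, 6.7 points, has a Monte Carlo standard error of about 2.5. A calculation from expected logistic information over 1,540 assumed configurations gave noncentrality ratios of 1.01 to 1.05 and gains of at most 2.1 points.

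**Step 6. Other structures.** These move the figures further from the stated pair.
- Random slope variance equal to the intercept variance (60 weeks, no gap): 98.5% at 0.01, 77.6% at 0.1.
- Cluster autocorrelation 0.8 (60 weeks, 8-week gap): 95.5% at 0.01, 79.9% at 0.1.
- Parallel-cluster design effect (40 weeks): 98.3% at 0.01, 38.6% at 0.1.

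**The case against.** **Power can rise with the ICC in a stepped-wedge trial.** This is correct, and the simulations in step 5 show it. The direction of the stated difference is therefore no error. The size remains unexplained: 15.7 points against a few attainable.

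**The bound is conditional.** It assumes a conventional ICC, fixed total variance and no other change between runs. The article does not say on which scale the correlation is defined, and the full protocol and simulation details are not shown. This stands as a limit on the conclusion. One alternative was tested: reading 0.20 and 0.113 as proportions for a typical team, so that total variance is not fixed. Within-team information then rises only 1.03-fold (latent scale) or 1.04-fold (proportion scale), which moves 79.3% to about 81%. If a further input did change, the paragraph does not say so and still needs correcting.

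**The figures were simply swapped.** A reader might infer this, and so conclude that base-case power is 79.3% and type II error about four times that stated (20.7% against 5%). The reversed pair is attainable, as step 6 shows, but only with a schedule and a cluster autocorrelation, or a slope variance tied to the correlation, that the article does not give. Meanwhile 95% at 0.1 is nearly reached without any such addition (94.1% in step 4), which would leave only the sensitivity figure wrong. The document cannot settle this.

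**The consequences may be small.** If only the sensitivity figure is wrong, the planned power stands. Design, outcome and analysis are unaffected in any case.

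**Conclusion.** Wrong as written. Under a conventional ICC with fixed total variance, and with only the correlation changed, 95% at 0.1 and 79.3% at 0.01 are incompatible: the pair needs a factor of 1.685 where at most 1.10 is available. No schedule or model tried gave both figures. At least one power is wrong, or an unstated input differs between the runs. Three explanations remain open: an error in the sensitivity figure alone, a transposition (base-case power then about 79%), or another changed input. The incompatibility does not depend on the missing figure; the absolute powers in steps 4 to 6 do.

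**What to change.** Recheck the simulation under the model in Analysis of primary outcome: team random intercept, random intervention slope, linear time, age and sex, with the Fig. 1 schedule. Run it at both correlations with everything else held fixed. Then correct whichever power is wrong, or state the other input that changed between the runs. No term beyond that model is needed for this check.

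The cost is a few hours of simulation and one corrected paragraph. Enrolment does not change. The only downside is that the stated base-case power may become less favourable.

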#### Statistical analyses

We will use R for data management, modelling and graphics [33]. We will make all our R code publicly available via GitHub. We will use EQUATOR guidelines to write-up our results, using the CONSORT guidelines for randomised trials, the extension for stepped-wedge trials [39, 40]. Additional details of the statistical analysis plan are provided online [37].

#### Analysis of primary outcome

The primary outcome, proportion of patients with at least one ICU admission, will be analysed using a mixed effects Binomial regression. The key variable is the timing of the switch from usual care exposure to intervention exposure phase. The intervention timing regression coefficient will be treated as a random slopes term to account for potential differences in intervention effects across clinical teams. A linear time covariate will be included to capture a potential calendar time trend. The model will also adjust for likely predictors of patient age and sex. The model will include a random intercept for each enrolled clinical team to account for any underlying differences in the proportion of patients with ICU admissions between the teams.

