**Fig. 2 Fig2:**
[figure not shown]
Schematic of the InterACT intervention to be implemented

For the purpose of this study, patients are considered to be in the at-risk population if they were identified to be *high-risk CriSTAL* and *SPICT-positive*. Patients are classified as *high-risk CriSTAL* (at high risk of death within 3 months) if they have a CriSTAL score of 6 or greater. Patients with a SPICT general indicator score of 2 or greater are considered *SPICT-positive* (presence of indicators of potential deterioration within 12 months).

Site based trained auditors will review patient records of new admissions to participating clinical team twice weekly to identify patients in the at-risk population. Record review data will be collected using an electronic form in REDCap [32].

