#### Randomisation, allocation and blinding

All three hospitals will receive the intervention, with the timing randomised. A statistician investigator ([name]) will be responsible for computer generation of the trial timing randomisation as per Fig. 1 and the intra-hospital clinical team identifiers. These identifiers will help anonymise the data storage and reporting.

Given the nature of the intervention and trial design, it is not possible to blind the clinical teams to the intervention. The intervention exposure phase commencement date will be concealed from the hospital teams during the site preparation and clinical team recruitment phase. Hospital teams will be notified of their intervention establishment and intervention exposure start dates about 8 weeks prior to allow time to plan for the intervention establishment phase activities.

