#### Analyses of secondary outcomes

Competing-risk proportional hazards survival models will be used to analyse time-to-event outcomes during patient hospitalisations (outcomes 2, 4, 5, 6 and 7). Hospital discharge and in-hospital deaths are treated as competing risks. Use of the competing risk survival model provides an estimate of the intervention effect which appropriately accounts for the competing and time-varying nature of discharge and death on the outcomes [41]. The models will have a binary variable indicating if patients were in the intervention exposure phase. The survival analysis will adjust for likely predictors of patient age, sex and time spent in hospital for identified hospital episode prior to admission to enrolled clinical team. The survival analysis will stratify by clinical teams to control for consistent differences between teams. Cumulative incidence curves will be used to compare the event rates over time between the usual care exposure and intervention exposure phases.

We will use a proportional hazards survival model to investigate the difference between usual care and intervention exposure phases in the time to re-admission within the first 12 weeks after index discharge (outcome 3). Patients who died after leaving hospital or were not re-admitted within the 12 weeks will be censored. Clinical teams will be included as strata.

Data on the health services used by patients during their hospital admission will be retrieved from the hospitals’ clinical costing database to evaluate changes in admission and treatment costs (outcome 8). Any costs that occurred before the patient was identified to be in the at-risk population will be excluded. Statistical distributions will be fitted to describe variability in all cost parameters. The key measure of cost will be the average cost per patient. This will be presented alongside 95% bootstrap confidence intervals to estimate the uncertainty in this average.

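### The primary model leaves out prior hospital time, which the survival models on the same patients adjust for, so a case-mix shift at crossover would be only partly corrected

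*Protocol article*

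**What the plan says.** Under Analysis of primary outcome, ICU admission is analysed by a mixed effects Binomial regression. Its patient-level covariates are stated in one sentence: "The model will also adjust for likely predictors of patient age and sex". The rest of the adjustment is for team and time: "The model will include a random intercept for each enrolled clinical team"; "The intervention timing regression coefficient will be treated as a random slopes term"; and "A linear time covariate will be included to capture a potential calendar time trend".

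Under Analyses of secondary outcomes, the models for outcomes 2, 4, 5, 6 and 7 have a longer list: "The survival analysis will adjust for likely predictors of patient age, sex and time spent in hospital for identified hospital episode prior to admission" to the enrolled team.

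Study outcomes says that outcomes 1 to 9 all concern patients found to be at risk on screening. Table 1 starts the clock for outcomes 1 and 2 at the same point, the date of first at-risk classification.

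On how that cohort arises, the Intervention section says: "Site based trained auditors will review patient records of new admissions to participating clinical team twice weekly". A patient enters with a CriSTAL score of at least 6 and a SPICT general-indicator score of at least 2. Under Randomisation, allocation and blinding: "it is not possible to blind the clinical teams to the intervention". The same section says hospitals learn their start dates about 8 weeks ahead. The Discussion says that teams within a site cross over simultaneously.

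**The concern.** The trial names prior hospital time as a likely predictor for one set of analyses and leaves it out of the analysis that decides the trial. Taken alone, that is an unexplained difference between two covariate lists.

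It matters because of how patients come into the analysis. They are not enrolled before allocation. They are flagged from clinical records while the hospital is in a known phase, by site-based auditors for whom no blinding is described. If documentation, referral patterns or flagging change when a hospital crosses over, the flagged patients after crossover may differ in ICU risk from those before it. All seven teams of a hospital switch together, so such a change would coincide with the intervention indicator. The random intercept removes stable team differences and the linear term removes gradual drift, but neither removes a step. The random slope lets the effect vary between teams without separating the effect from such a step. Age and sex correct it only so far as it runs through age and sex.

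**Working it through.** **1. The two covariate lists.**

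| | Primary model (outcome 1) | Survival models (outcomes 2, 4–7) |
|---|---|---|
| Patients | flagged at risk | flagged at risk |
| Age, sex | yes | yes |
| Prior hospital time | no | yes |
| Team | random intercept and slope | strata |

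Outcome 2 is analysed in the same patients as outcome 1, so prior hospital time is needed for all of them. That it is available for everyone is inferred from this, not stated. It is fixed before the enrolled team admits the patient, and so before that team receives feedback on the patient.

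**2. The plan's own power figure.** The article states 95% power for 0.20 against 0.113, with 21 teams, 3 patients per team-week, within-ward correlation 0.1 and two-sided 5%. The check used generalised least squares on team-week means.
- Mean risk (0.20 + 0.113)/2 = 0.1565, so V = 0.1565 × 0.8435 = 0.132.
- Between-team variance 0.1 × 0.132 = 0.0132. Variance of a team-week mean 0.9 × 0.132/3 = 0.0396.
- Power = Φ(0.087/SE − 1.96).

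Phase lengths are in Fig. 1, which was not available, so four layouts were assumed. With a linear time term they give 83.7% to 98.4% without a random slope, and 78.8% to 95.5% with a slope SD of 0.05 on the risk scale. The stated 95% is attainable but cannot be confirmed.

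**3. What one more covariate gains.** No document gives the prognostic strength of prior hospital time, CriSTAL or SPICT, so a generic standard-normal covariate was simulated over a range.
- Layout (assumed): usual care 10/20/30 weeks, 6-week establishment, end at week 52, 2,898 patients.
- Model (assumed): logistic link, linear time, team indicators standing in for the random intercept, no random slope. Team variance on the logit scale (0.1/0.9) × π²/3 = 0.366.
- 300 simulations per row; Monte Carlo error √(0.85 × 0.15/300) ≈ 2 points.

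| OR per SD | Power without | Power with | SE of log OR without | with |
|---|---|---|---|---|
| 1.0 | 85.0% | 85.0% | 0.231 | 0.231 |
| 1.2 | 85.3% | 86.7% | 0.233 | 0.234 |
| 1.5 | 88.0% | 88.0% | 0.233 | 0.236 |
| 2.0 | 85.0% | 87.0% | 0.231 | 0.239 |

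The SE does not fall. The gain is 0 to 2 points, within simulation error.

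**4. What a shift at crossover does.** Here there is no true effect, and the covariate mean moves by 0.1 or 0.2 SD (assumed) when the hospital crosses over. The approximate spurious odds ratio is (OR per SD)^shift. There were 400 simulations per row; Monte Carlo error is about 1.1 points at 5% and 1.5 points at 10%.

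| OR per SD | Shift (SD) | Spurious OR | Type I error unadjusted | adjusted |
|---|---|---|---|---|
| 1.2 | 0.1 | 1.02 | 4.0% | 3.5% |
| 1.2 | 0.2 | 1.04 | 4.5% | 4.5% |
| 1.5 | 0.1 | 1.04 | 6.2% | 5.0% |
| 1.5 | 0.2 | 1.08 | 5.2% | 3.7% |
| 2.0 | 0.1 | 1.07 | 8.5% | 4.0% |
| 2.0 | 0.2 | 1.15 | 10.2% | 5.2% |

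For scale, the design effect is ln(0.113/0.887) − ln(0.20/0.80) = −0.674. The spurious log odds ratio runs from 0.1 × ln 1.2 = 0.018 (3% of 0.674) to 0.2 × ln 2 = 0.139 (21%). A shift towards lower-risk patients would have the opposite sign and would favour the intervention.

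The adjusted column assumes that the shift runs wholly through the added covariate and that the covariate is measured alike in both phases.

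**The case against.** Pre-specified adjustment for age and sex is legitimate, and the model also handles stable team differences and linear drift. The article refers to an online analysis plan that may hold further covariates or sensitivity analyses. Elapsed stay bears directly on a time-to-event scale, so a different list for a binary outcome is not in itself a contradiction. All of this stands, and it keeps the point modest. It does not explain why a variable the trial calls a likely predictor in these patients is absent from the published primary model.

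A reader might infer three stronger things that the documents do not support.

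- *That real precision is being wasted.* Applying √(1 − R²) with R² of 0.05 to 0.10 would suggest an SE 2.5 to 5% smaller. That is a linear-model result. In the logistic simulation the SE did not fall. Selecting on CriSTAL and SPICT thresholds also narrows the remaining spread of those scores.
- *That CriSTAL and SPICT belong in the primary model.* They are scored from records that could themselves change with phase. If fuller notes raise scores at unchanged true risk, adjusting for them can introduce bias. Adjustment also cannot fully undo selection on the same scores.
- *That the model should be rerun on all screened patients.* Outcome 1 is counted from the date of first at-risk classification, which unflagged patients lack. Such a rerun needs a new outcome definition and extra linkage, and it would dilute the effect.

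Nor do the documents show that flagging will differ by phase: the thresholds are fixed and no phase-specific screening procedure is described.

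**Conclusion.** The point holds as a modest weakness in the covariate choice, not as an error that invalidates the primary analysis. Age and sex are the only patient-level covariates for the primary outcome, while the survival models on the same patients add prior hospital time. The article gives no reason. A case-mix step at crossover would be only partly corrected.

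The precision gain from adjustment is about 0 to 2 power points. The protection against bias matters only if a strong predictor shifts at crossover. With an odds ratio of 1.2 to 1.5 per SD, unadjusted type I error stayed at about 4 to 6%. At 2.0 per SD it reached about 9 to 10%, against 4 to 5% adjusted. These sizes rest on an assumed layout, assumed covariate strengths and an assumed shift. The documents supply none of the three.

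**What to change.** 1. Add prior hospital time to the primary model, defined as in the survival models: "time spent in hospital for identified hospital episode prior to admission to enrolled clinical team". If it is left out on purpose, state the reason. The survival analyses already require the variable, so this costs nothing in data collection.
2. Pre-specify a sensitivity analysis that also adds the CriSTAL score and SPICT general-indicator count from the first at-risk screening. State that scoring could itself change with phase, so agreement with the primary result is reassuring but disagreement has more than one explanation. Both scores are obtained at screening.
3. Report numbers screened and proportion flagged at risk, by team and phase. Screening already generates these counts, and they are the direct check on whether the cohort changed at crossover.

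Items 1 and 2 should be fixed before outcome data are linked.
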